### 7.3 PLANNED ANALYSES

All individual values will be listed and standard statistical parameters (number of non-missing values, mean, standard deviation, median, quartiles and range) or frequency tables will be calculated separately for each treatment group (including the respective totals). The data recorded will be used to check whether the study protocol has been adhered to (e.g., inclusion and exclusion criteria, visit schedules etc.). Data from subjects that withdraw after the screening period and prior to Visit 3 will not be reported.

The statistical analysis will be based on the following populations:

- Treated Set (TS): The treated set (TS) will consist of all subjects who were treated with at least one dose of study drug.
- Full Analysis Set for Renal (FAS\_RENAL): The full analysis set (FAS\_RENAL) will consist of all subjects who were treated with study drug, have a baseline measurement and an evaluable post-dosing renal data under the clamped hyperglycaemia condition (Visit 13) for the primary endpoint.
- Full Analysis Set for Diabetes Mellitus (FAS\_T1DM): The full analysis set (FAS\_T1DM) will consist of all subjects who were treated with study drug, have a baseline measurement and an evaluable post-dosing diabetes mellitus data for the other endpoints.

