| 13:30-14:00 | Repeat measurements of MAP, GFR, ERPF, FF, RBF and RVR (all average of 2 measurements), RAAS mediators, NO, prostanoids, arterial stiffness and markers of sympathetic nervous system activation (heart rate variability and circulating plasma levels of adrenaline/noradrenaline) and other laboratory assessments.                                                                  |

- E. In addition to the required ECG at Visit 1 and Visit 13, additional ECGs should be performed in cases of cardiac symptoms (rhythm disorders or cardiac ischemia).
- F. Subjects will be advised to follow a healthy diet and exercise program based on investigator recommendations during the study except during the 7 days preceding the start of renal physiology laboratory assessments when they will be instructed to follow a modified diet, refer to G below for details.
- G. Subject will be instructed to adhere to a high-sodium (preferably > 140 mmol/day) and moderate-protein (<1.5g/kg/day) diet during the 7 days preceding the start of renal assessments at baseline during Visits 3 and 4 (the diet to continue until the end of renal assessments at baseline, Visit 4) and during the 7 days preceding the start of the end of treatment renal assessments during Visits 12 and 13 (the diet to continue until the end of renal assessments). The initial 8-point HBGM must be performed prior to start of the modified diet (i.e. prior to day -7). If a subject fails to adhere to the prescribed high-sodium and moderate-protein diet, the investigator will assess whether the subject is still eligible to start the renal assessments based on the subject's actual diet during the 7 days preceding Visit 3. In cases of an unsatisfactory diet, subjects may have to be screen failed based on the investigator's judgement.

Proprietary confidential information.

© 2012 Boehringer Ingelheim International GmbH or one or more of its affiliated companies. All rights reserved.

This document may not - in full or in part - be passed on, reproduced, published or otherwise used without prior written permission.

- H. A local pregnancy test will be done in women of child bearing potential. More frequent testing can be done if required by the local regulation and/or authority or per investigator judgement.

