### **3.3.4 Removal of subjects from therapy or assessments**

#### **3.3.4.1 Removal of individual subjects**

An individual subject is to be withdrawn from the trial if:

- The subject withdraws consent, without the need to justify the decision
- The subject needs to take concomitant drugs that interfere with the investigational product or planned study assessments
- The subject is no longer able to participate for other medical reasons (e.g. surgery, AEs or other diseases)
- Occurrence of hypoglycaemia that may put the subject at risk with continued participation (e.g. repeated hypoglycaemic episodes) based on investigator judgement
- If a subject becomes pregnant during the trial the investigational drug will be stopped, the subject will be discontinued from the trial and the subject will be followed up until birth or otherwise termination of the pregnancy.

A subject can be discontinued after discussion between sponsor and investigator if eligibility criteria are being violated, or if the subject fails to comply with the protocol (e.g. non-attendance at study assessments).

Subjects who drop out during the screening phase and before the start of treatment with BI 10773 (study Day 3) will be considered as screening failures. They have to be recorded as a screening failure in the electronic Case Report Forms (eCRFs) and no further follow-up is required.

Subjects who discontinue or withdraw from the study after study Day 3 (after the start of therapy) will be considered as “early discontinuations” and the reason for premature discontinuation will be recorded in the eCRFs. Subjects who discontinue prematurely (before completion of Visit 13) will be replaced in order to obtain at least 12 subjects in the hyperfilterer group and 12 in the non-hyperfilterer group who complete the treatment phase of the study (Visit 13). The data for screen failures will be included in the trial database and will be reported. A new antidiabetic medication regimen can be started immediately after discontinuation, if determined by the investigator as necessary for subject safety. This must be recorded in the eCRFs.

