#### 5.2.2.2 Adverse event and serious adverse event reporting

All adverse events, serious and non-serious, occurring during the course of the clinical trial (i.e., from signing the informed consent onwards through the observational phase) will be collected, documented and reported to the sponsor by the investigator on the appropriate CRFs / eCRFs / SAE reporting forms. Reporting will be done according to the specific definitions and instructions detailed in the 'Adverse Event Reporting' section of the Investigator Site File.

For each AE, the investigator will provide the onset date, end date, intensity, treatment required, outcome, seriousness, and action taken with the investigational drug. The investigator will determine the relationship of the investigational drug to all AEs as defined in Section 5.2.2.1.

Clinically relevant abnormalities found during the physical examination at Visit 1 (including abnormalities with vital signs or ECG) will be considered to have already existed prior to signing of informed consent and therefore should be considered baseline conditions instead of adverse events, unless there is good reason to assume that they first appeared after signing of informed consent.

The investigator also has the responsibility to report AEs occurring within one week after a subject completes the trial. Any AEs reported to the sponsor during this period must be documented in the safety database.

If not stipulated differently in the ISF, the investigator must report the following events via telephone/fax using the SAE form immediately (within 24 hours or the next business day whichever is shorter) to the sponsor: SAEs and non-serious AEs occurring at the same time as an SAE and/or which are medically related to the SAE(s), and protocol-specified significant events. With receipt of any further information to these events, a follow-up SAE report has to be provided. SAEs and non-serious AEs must include a causal relationship assessment made by the investigator.

The SAE form is to be forwarded to the defined unique entry point identified for the BI OPU (country-specific contact details will be provided in the ISF). This immediate report is required irrespective of whether the investigational product has been administered or not and irrespective of causal relationship. It also applies if new information to existing SAEs or protocol-specified significant events becomes available.

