##### Run-in (Visit 2)

- Visit 2 should preferably occur within 7 days of Visit 1 once it has been confirmed that the subject is eligible to continue to Visit 2. Visit 2 assessments will be performed as noted in the study Flow Chart. Labs to be done in a fasted state.
- Those subjects who qualify at screening (as determined at Visit 1), will undergo a 2 week open-label placebo run-in period (Visit 2 to Visit 3).
- Subject will be expected to take the run-in medication (placebo) once daily as described in Section 4.1.4. From the start of the run-in period, all eligible subjects will

Proprietary confidential information.

start CGM (using the Guardian® REAL-Time CGM System) and will continue the monitoring process until Visit 15 (last clinic visit). Subject must be instructed on the proper use of the Guardian® REAL-Time CGM System including the set up and daily calibration of the CGM components. Subjects should be contacted preferably daily or every 3-6 days during the run-in phase to ensure that they are performing study procedures and CGM calibrations adequately.

- A home blood glucose meter and all the necessary supplies will be given to subjects, including a fasting plasma glucose log (to be completed daily) and an 8-point glucose log (to be completed as specified in the study Flow Chart). All logs will be included in a subject study diary. HBGM will be done according to Section 5.3.2 and based on the Flow Chart.
- *Subjects must be reminded that all insulin dose evaluations and adjustments (basal and bolus) must be based on fingerstick blood glucose determinations using the supplied home blood glucose meter.* Subject must not adjust insulin therapy based on CGM values.
- Subjects will also be instructed to follow a healthy diet and exercise program during the course of the study as noted in the study Flow Chart, apart from the 7 days prior to renal assessments (at Visit 3-4 and Visit 12-13) in which case they will be prescribed a specific a high-sodium (preferably > 140 mmol/day) and moderate-protein (< 1.5 g/kg/day) diet during the 7 days preceding the start of renal assessments at baseline during Visits 3 and 4 (the diet to continue until the end of renal assessments at baseline, Visit 4) and during the 7 days preceding the start of the end of treatment renal assessments during Visits 12 and 13 (the diet to continue until the end of renal assessments).

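### Sections 3.3.4.1 and 7.3 give opposite reporting rules for subjects who withdraw during the placebo run-in

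*Protocol*

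**What the plan says.** Section 3.3.4.1 (Removal of individual subjects) sets the class for those that "drop out during the screening phase and before the start of treatment with BI 10773 (study Day 3) will be considered as screening failures". It adds: "The data for screen failures will be included in the trial database and will be reported".

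Section 7.3 (Planned analyses) states: "Data from subjects that withdraw after the screening period and prior to Visit 3 will not be reported".

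Three other places fix the timing and the terms:

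- The Flow Chart shows screening (Visit 1) and placebo run-in (Visit 2) as separate periods. Section 6.2.1 says that subjects who qualify at Visit 1 "will undergo a 2 week open-label placebo run-in period (Visit 2 to Visit 3").
- Flow Chart footnote G deals with the diet in the seven days before Visit 3: "In cases of an unsatisfactory diet, subjects may have to be screen failed".
- Section 5.2.2.2 requires adverse events to be collected "from signing the informed consent onwards through the observational phase".

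**The concern.** Both statements are current text, and both reach a subject who withdraws between Visit 2 and Visit 3. One says that the data are reported and the other that they are not. An analysis plan written under this protocol cannot comply with both.

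What is at stake is the completeness of the trial report. The run-in is an active part of the trial. Subjects take placebo tablets daily, wear the CGM sensor, may have their insulin adjusted (Section 4.2.1 encourages treatment to target) and follow a prescribed diet in its last week. Section 3.1 counts a subject as included once consent is signed. If Section 7.3 is followed, a subject can be included, have an adverse event in the run-in, withdraw, and appear in no table or listing.

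**Working it through.** No figure in the plan needs reproducing. The check compares the rules by the time at which a subject leaves, and then bounds the number affected.

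**Step 1. Timeline (Flow Chart, Section 4.1.4).** Visit 1 is Day -21, Visit 2 is Day -14, Visit 3 is Day 1, Visit 4 is Day 2, and the first BI 10773 dose is on Day 3.

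**Step 2. Rule by time of leaving.**

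| Subject leaves | Section 3.3.4.1 | Section 7.3 sentence |
|---|---|---|
| After Visit 1, before Visit 2 | Screening failure, reported | Does not apply |
| Visit 2 to before Visit 3 (run-in) | Screening failure, reported | Not reported |
| Visit 3 to before the first dose on Day 3 | Screening failure, reported | Does not apply |
| After Day 3 | Early discontinuation, reason recorded | Does not apply |

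The conflict is confined to the second row. Section 7.3 therefore removes one middle segment of the disposition, while the segments before and after it stay reportable.

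**Step 3. Does Section 3.3.4.1 really cover the run-in?** Its wording mentions the screening phase, so this needs checking. Three points say that it does:

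- The class is stated to run up to the start of BI 10773 on Day 3, which is later than the end of the run-in.
- Footnote G uses the term screen failed for a failure to follow the run-in diet.
- The only other class starts later: "Subjects who discontinue or withdraw from the study after study Day 3 (after the start of therapy) will be considered as" early discontinuations. If run-in dropouts were not screening failures, they would have no class at all.

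**Step 4. Would another rule bring these subjects into the report?** Section 7.3.3 bases the safety analysis on the treated set, which needs at least one dose of study drug. Section 4.1.4 puts the first dose of study medication on Day 3, so the natural reading leaves out subjects who took only run-in placebo. The treated-set definition does not say so explicitly. On that reading, whether these subjects appear in the report depends on which of the two conflicting sentences is followed.

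**Step 5. Number affected.** Section 3.3 plans for about 45 screened and 30 entered: 45 - 30 = 15 not entered. These 15 include failures at Visit 1 and any dropouts between Visit 3 and Day 3, and the Section 7.3 sentence applies to neither. The protocol does not split them. On planning figures, the number under the conflicting rules is between 0 and 15.

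**The case against.** The best defence is that the screening phase in Section 3.3.4.1 means Visit 1 only. The Flow Chart separates screening from run-in, and Section 6.2.1 has subjects qualify at screening before the run-in starts. On that reading the two rules do not overlap. The reading is possible but weak, for the three reasons in step 3 of the working. It also leaves the practical problem in place: Section 7.3 would still keep run-in withdrawals out of the report while failures at Visit 1 are reported.

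A second defence is that disposition tables and listings belong in the statistical analysis plan. Their layout does. But the protocol itself states both rules, and an analysis plan can follow one only by departing from the other.

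The rest of the defence concerns stronger readings that a reader might infer, and there it succeeds:

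- **Run-in events are lost altogether.** They are not. Section 5.2.2.2 has them collected and sent to the sponsor from consent, and Section 3.3 keeps a site log of all consented subjects. The gap is in the trial report.
- **Exclusions for poor compliance or diet are hidden, so the selection of the treated group is concealed.** The placebo tablet count is done at Visit 3. Diet is judged on the full seven days before Visit 3, and the 24-hour urine collection ends that morning. These decisions would mostly fall at Visit 3, outside the Section 7.3 interval. Footnote G also calls the diet exclusion a screen failure, which Section 3.3.4.1 reports.
- **Subjects who leave after a clamp at Visit 3 or 4 get no safety follow-up.** Section 3.3.4.1 does say "They have to be recorded as a screening failure in the electronic Case Report Forms (eCRFs) and no further follow-up is required". Read beside the paragraphs on early discontinuations, this most naturally means the end-of-treatment and Visit 15 assessments. It does not cancel the adverse event duties in Sections 3.1 and 5.2.2.2. These subjects also leave after the Section 7.3 interval has ended.
- **A third of those screened would go unreported.** The figure of 15 counts everyone not entered, including failures at Visit 1, so it is an upper bound and not an estimate.

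**Conclusion.** The point holds as an internal inconsistency with a narrow scope. For subjects who withdraw between Visit 2 and Visit 3, Sections 3.3.4.1 and 7.3 give conflicting instructions. If Section 7.3 is followed, their withdrawals and adverse events are left out of the trial report.

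The size is unknown: between 0 and 15 of about 45 screened on the planning figures, with nothing in the protocol to narrow it. No efficacy result changes. FAS_RENAL requires treatment with study drug and evaluable Visit 13 data, so no run-in dropout could contribute to the GFR analyses under either rule.

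The conclusion assumes that the screening-failure class in Section 3.3.4.1 extends through the run-in, which the protocol's own usage supports. If it does not, the formal contradiction goes, but run-in withdrawals remain unreported and without a class. Either way the Section 7.3 sentence should be corrected.

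**What to change.** Delete the sentence in Section 7.3, or replace it with one that agrees with Section 3.3.4.1. For example: *All consented subjects who withdraw before the first dose of BI 10773 are reported in the disposition summary by period (screening, run-in, Visit 3 to first dose) with the reason, and their adverse events from consent onwards are listed.* In Section 3.3.4.1, state that the screening-failure class includes the run-in and lasts until the first BI 10773 dose. The layout of the table and listing can be left to the analysis plan.

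The cost is a sentence in each of two sections, some rows in the disposition table and one short listing. No new data are needed: Section 3.3.4.1 already puts screen-failure data in the database, and Section 5.2.2.2 already collects the adverse events.

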##### Visit 4 (Day 2, Non-Fasted):

- Renal panel (clamped hyperglycaemia condition)

For symptomatic hypoglycaemic events the pre-treatment period is defined as the 2 week run-in period. For time spent in CGM-defined hypoglycaemia, the pre-treatment period is defined as the 2 week of CGM assessment during the run-in phase. Visit 3 renal measurements and Visit 4 renal measurements are respectively baseline measurements for Visit 12 and 13.

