## **7.2 NULL AND ALTERNATIVE HYPOTHESES**

The following primary hypotheses will be tested using a one-tailed test at an alpha level of 0.025. The basic hypothesis to be tested is:

$$H_0: \mu_d = 0 \quad \text{vs.} \quad H_1: \mu_d > 0,$$

where  $\mu_d$  is the mean change from baseline response after 8 weeks of treatment of BI 10773.

Since this is an exploratory study no adjustment in the alpha will be necessary.

Proprietary confidential information.

© 2012 Boehringer Ingelheim International GmbH or one or more of its affiliated companies. All rights reserved.

This document may not - in full or in part - be passed on, reproduced, published or otherwise used without prior written permission.

Hypothesis 1 under hyperglycaemia:

1.  $H_{01}$ : For hyperfilterer subjects, there is no change in GFR under the clamped hyperglycaemia condition after 8 weeks of treatment with BI 10773 (25 mg QD).
2.  $H_{11}$ : For hyperfilterer subjects, there is a decrease in GFR under the clamped hyperglycaemia condition after 8 weeks of treatment with BI 10773 (25 mg QD).

Hypothesis 2 under euglycaemia:

3.  $H_{02}$ : For hyperfilterer subjects, there is no change in GFR under the clamped euglycaemia condition after 8 weeks of treatment with BI 10773 (25 mg QD).
4.  $H_{12}$ : For hyperfilterer subjects, there is a decrease in GFR under the clamped euglycaemia condition after 8 weeks of treatment with BI 10773 (25 mg QD).

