#### 7.3.1 Primary analysis

Paired t-tests will be performed to test the difference in the GFR response between baseline and after treatment of BI 10773 (25 mg QD) in hyperfilterer subjects under separate

Proprietary confidential information.

© 2012 Boehringer Ingelheim International GmbH or one or more of its affiliated companies. All rights reserved.

This document may not - in full or in part - be passed on, reproduced, published or otherwise used without prior written permission.

conditions of controlled euglycaemia and hyperglycaemia. The primary analysis will be performed on the FAS\_RENAL.

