### **7.4 HANDLING OF MISSING DATA**

No special computations (e.g., interpolation, last value carried forward or similar) will be performed for the missing data.

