### **7.6 DETERMINATION OF SAMPLE SIZE**

For this trial, between-group analysis and within-group analysis will be performed. The sample size calculations are based on the between-group analysis. Listed below in [Table 7.6: 1](#) are the sample size calculations based on a two-group t-test (two-sided,  $\alpha=0.05$ ), which looks at the difference between the hyperfilterer and non-hyperfilterer groups.

With the sample size of 12 subjects per group and assuming that the standard deviation is 5, a two-group t-test with a 0.05 two-sided significance level will have 80% power to detect a difference in the means of 6 (i.e., the difference between group 1 (Hyperfilterer) mean and Group 2 (Non-hyperfilterer) mean). If the standard deviation is increased to 6, a sample size of 17 subjects per group would be required. As such, a minimum of 12 subjects per group will need to complete the trial (Visit 13) and therefore approximately 30 subjects will need to be entered to achieve the sample size requirements.

Proprietary confidential information.

© 2012 Boehringer Ingelheim International GmbH or one or more of its affiliated companies. All rights reserved.

This document may not - in full or in part - be passed on, reproduced, published or otherwise used without prior written permission.

Table 7.6: 1 Sample size calculations based on a two-group t-test (two-sided,  $\alpha=0.05$ )

| Mean Change
for
Hyperfilterer
Group | Mean Change
for Non-
hyperfilterer
Group | Difference
between the
groups | Standard
Deviation | Power
(%) | N
per group |
|----------------------------------------------|---------------------------------------------------|-------------------------------------|-----------------------|--------------|----------------|
| 8                                            | 5                                                 | 3                                   | 3.5                   | 80           | 23             |
| 8                                            | 5                                                 | 3                                   | 5                     | 80           | 45             |
| 8                                            | 5                                                 | 3                                   | 6                     | 80           | 64             |

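### One renal analysis set tied to Visit 13 serves both clamp conditions, so a valid euglycaemic GFR pair can be dropped because of a later, unrelated hyperglycaemic result

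*Protocol*

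**What the plan says.** Section 7.2 sets two separate primary hypotheses in hyperfilterers, one per clamp condition, each "tested using a one-tailed test at an alpha level of 0.025". The euglycaemic alternative reads "For hyperfilterer subjects, there is a decrease in GFR under the clamped euglycaemia condition after 8 weeks of treatment with BI 10773 (25 mg QD".

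Section 7.1 fixes the pairing: "Visit 3 renal measurements and Visit 4 renal measurements are respectively baseline measurements for Visit 12 and 13". Euglycaemia is therefore Visit 3 against Visit 12, and hyperglycaemia is Visit 4 against Visit 13.

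Section 7.3 defines FAS_RENAL as treated subjects with a baseline measurement, of which the visit is not stated, and "evaluable post-dosing renal data under the clamped hyperglycaemia condition (Visit 13) for the primary endpoint". Section 7.3.1 runs both primary tests on FAS_RENAL: "conditions of controlled euglycaemia and hyperglycaemia. The primary analysis will be performed on the FAS". Sections 7.3.2.1 and 7.3.2.2 use the same set for the secondary GFR analyses and the other renal endpoints. Section 7.4 adds: "No special computations (e.g., interpolation, last value carried forward or similar) will be performed for the missing data".

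On numbers, section 7.6 says "a minimum of 12 subjects per group will need to complete the trial (Visit 13". Section 3.3.4.1 replaces subjects who discontinue before completing Visit 13.

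**The concern.** The two conditions are analysed separately, but entry to the shared set depends on one of them. The euglycaemia test uses nothing from Visit 13, yet a subject whose Visit 13 clamp or inulin measurement fails, or who stops after Visit 12, leaves that test. The outcome of interest was already in hand when the excluding event occurred.

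Two things are at stake. The first is avoidable loss of data in groups of about 12. The second is that membership of a primary analysis depends on something that happens after treatment and after the outcome, and that event need not be random (an adverse event around Visit 12, for example). The same rule removes valid Visit 12 values of the other renal endpoints, since it is GFR at Visit 13 that decides membership.

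**Working it through.** **What each test needs and what the set asks for**

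| Test | Needs | FAS_RENAL asks for | Mismatch |
|---|---|---|---|
| Euglycaemia | Visits 3 and 12 | a baseline, Visit 13 | Visit 12 not asked for; Visit 13 asked for but not used |
| Hyperglycaemia | Visits 4 and 13 | a baseline, Visit 13 | baseline visit not named |

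Taking the possible single failures in turn:

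- Visit 13 fails: the Visit 3/Visit 12 pair is valid but the subject is outside the set. The pair is lost.
- Visit 12 fails: the subject is in the set and supplies the Visit 4/Visit 13 pair, but no euglycaemic pair.
- Visit 4 fails: Visit 3 can serve as the baseline measurement, so the subject is in the set and supplies the Visit 3/Visit 12 pair only.
- Visit 3 fails: the group is defined by the Visit 3 GFR (sections 3.2, 3.3, 5.2.3 and 7.1), so the subject cannot be classed and does not count towards either group.

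**Inputs.** 12 per group, SD 5, difference 6, two-sided 0.05 (section 7.6); hyperfilterer mean changes of 8 to 11 and SDs of 3.5 to 8 (Table 7.6: 1); one-sided 0.025 for the paired tests (section 7.2). I take the SD to be that of the individual change from baseline.

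**1. The plan's own figure.** The plan states that "a two-group t-test with a 0.05 two-sided significance level will have 80% power to detect a difference in the means of 6". For a two-sample t-test the noncentrality is difference / (SD x sqrt(2/n)).

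- n = 12: 6 / (5 x sqrt(2/12)) = 2.94 on 22 df, power 80.2%. The stated 12 is reproduced, as are all ten rows of Table 7.6: 1.
- n = 11 in both groups: 6 / (5 x sqrt(2/11)) = 2.81 on 20 df, power 76.3%.
- 11 against 12: power 78.3%.

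**2. Precision of the paired test.** Half-width = t(0.975, n-1) x SD / sqrt(n).

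- n = 12: 2.201 x 5 / sqrt(12) = 3.18.
- n = 11: 2.228 x 5 / sqrt(11) = 3.36, which is 3.36/3.18 = 1.06 times as wide.

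**3. Power of the paired test.** One-sample noncentral t, one-sided 0.025, for the smallest planned hyperfilterer change (8):

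| SD | n = 12 | n = 11 |
|---|---|---|
| 5 | 99.9% | 99.7% |
| 6 | 98.7% | 97.8% |
| 8 | 88.3% | 84.8% |

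For a change of 11, power at n = 11 is 98.3% or more at all three SDs.

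**4. How many pairs might be lost.** The protocol gives no rate of non-evaluable measurements. The rates p below are assumptions, with visits taken as independent. The expected number of valid Visit 12 results discarded because Visit 13 fails is 12 x p x (1-p). The chance that 12 completers yield fewer than 12 evaluable results in one condition is 1 - (1-p)^12.

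| Assumed p | Expected Visit 12 results discarded, of 12 | Chance of fewer than 12 |
|---|---|---|
| 2% | 0.24 | 22% |
| 5% | 0.57 | 46% |
| 10% | 1.08 | 72% |
| 15% | 1.53 | 86% |

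**The case against.** The exposure is narrow. The Flow Chart puts Visit 13 one day after Visit 12, and a subject who stops between them is replaced, so the count of 12 is protected in that case. About 30 subjects are to be entered for a minimum of 24 completers, so 12 is a floor. The trial is exploratory, and at the planned changes the primary paired test has power to spare. All of this stands and limits the size of the point. It does not touch the logic: the replaced subject's valid euglycaemic pair is still discarded, as is that of a completer whose Visit 13 measurement fails.

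It could also be said that one set keeps the same subjects in both tests. The current definition does not achieve that. A subject without a usable Visit 12 value is in FAS_RENAL but, with no imputation, cannot enter the euglycaemia t-test.

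Two stronger readings are tempting. A reader might infer that a completer with a failed Visit 3, 4 or 12 measurement counts towards the 12 yet contributes nothing. The pairing rule contradicts this: a failure at Visit 4 or Visit 12 costs one condition's pair and leaves the other, and a failure at Visit 3 leaves the subject unclassified and so uncounted. A reader might also infer that the minimum must be recounted in evaluable pairs. That would change the stopping and replacement rules. Since section 3.2 expects GFR results only 3-4 weeks after Visit 3, it could also mean treating more subjects while results are pending. Nothing in the protocol shows a shortfall that would justify it.

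**Conclusion.** The definition of FAS_RENAL does not fit the euglycaemia analyses that it serves and should be changed. The case rests on the text of sections 7.1 to 7.3 and needs no assumption.

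The numerical effect is probably small. One lost pair of 12 costs about 6% in interval width at SD 5. The primary test is not put at risk at SD 5 or 6; only at SD 8 with the smallest planned change does one lost pair cost a few points of power (88.3% to 84.8%). Larger losses would need several failures in a group of 12, and the protocol gives no rate that would support them.

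A secondary consequence concerns the sample size statement. Twelve completers per group can yield fewer than 12 evaluable pairs in a condition, and the between-group calculation has no margin: 80.2% at 12 per group, 76.3% at 11. These figures follow the two-group t-test of section 7.6; the planned between-group analysis is an ANCOVA, for which the protocol gives no separate calculation.

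**What to change.** - In section 7.3, define the renal set by condition and endpoint: treated subjects with evaluable values at Visits 3 and 12 for euglycaemia, or at Visits 4 and 13 for hyperglycaemia. Note that any analysis by filtration group also needs the Visit 3 GFR for classification.
- Apply this to the primary, secondary and other renal analyses. Keep the current FAS_RENAL as a sensitivity analysis, and report n for each test.
- In section 7.6, state that 12 completers per group do not guarantee 12 evaluable pairs in each condition, and give the between-group power at 11 per group (about 76%). Leave the recruitment and replacement rules as they are.

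The cost is a wording change with no new data and no extra subjects. The downside is that the two primary tests may rest on slightly different subjects, which the reported n will make visible.
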